##### Data quality assurance mechanisms

At enrolment, quantitative data will be collected by 10 research assistants with a minimum of a diploma degree. The research assistants undergo a 5-day training on data collection, which will focus on basic research ethics and study procedures.

##### Outcomes

The primary outcome of this study is the contraceptive discontinuation rate among the family planning users at 12 months. Participants will be considered to have discontinued if they report not using their baseline method during the follow-up interviews. Participants who discontinue use of the method used at the time on enrollment and initiate use of different method within one month will be considered to have switched methods. Other secondary outcome measures include discontinuation at 3, 6, and 24 months; the method information index [11] will be used as a proxy for quality of family planning counseling.

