Kenya’s modern contraceptive use among married women is 53%, with an unmet need of family planning of 18% and a total fertility rate of 3.9, as per the last DHS of 2014 [9]. The more recent PMA 2020 round 7 data from 2018 indicates a further increase in the modern contraceptive prevalence rate (mCPR) to 60.7% and a reduction in unmet need to 13.8% [10]. Despite the improvement in contraceptive use, discontinuation rates have remained higher over the last three decades with one out three women discontinuing use by 12 months [9]. Contraceptive continuation rates has been suggested as a useful summary measure of the overall effectiveness of program services in enabling clients to sustain contraceptive use even though they may switch from one method to another [11, 12]. The PMA 2020 round of surveys have shown that there is still a huge gap in provision of quality of family planning services at the health facility and community levels, with only 67% of the women informed of other methods, 59% counseled on side effects, and 54% told what to do when they experience the side effects, thus presenting missed opportunities for provision of quality family planning services that might promote continuation or method switching [10].

In Kenya, as in other lower-middle income countries, the national health management information system does not monitor contraceptive continuation at the facility level, as the data capture mechanism is not longitudinal. More so, within the health system, only users of reversible methods, including implants and IUDs, go back to a facility, since they require a clinical intervention during removal of these methods. Users of short-term methods, like condoms, pills, and injectables, simply fail to turn up for their next appointment for resupply. Therefore, tracking contraceptive discontinuation and method switching is limited to use of survey data such as a DHS that collects calendar data on women’s history of contraceptive use.

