##### Participant follow-up

Participants will be enrolled for 24 months. Data on current method use, side effects and complications, fertility intentions, satisfaction, motivation, and decision-making, including male partner involvement on contraceptive use, will be collected at five different points in time to assess the dynamics of contraceptive use, either continuation, discontinuation, or switching. Data collection will occur the following time points: at baseline and at 3, 6, 12, and 24 months (Fig. 1). At baseline, individuals who are eligible to participate and have consented to be part of the study, will complete an online questionnaire, which will be more extensive (the questionnaire is described in more detail below), prior to leaving the health facility. Participants will provide their phone contact information to enable the research team to get in touch in the subsequent follow-up period for brief interview sessions. During each follow-up interview, consent will be sought to ensure the participants are still interested in participating in the study. During each round of follow-up interviews, three attempts will be made to contact participants before a determination of loss to follow-up is made. The second and third round of interviews will take place at 3 and 6 months after baseline, because women who choose some short-term methods will require a 3-month cycle for resupply. The follow-up at 12 months will be used to determine the contraceptive continuation rate, which is the primary outcome for this study. The 12 and 24 months’ period allows comparisons with other surveys, including the DHS, that have used the same time reference to report discontinuation.

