##### Questionnaire

The baseline questionnaire has five sections: the first section covers socio-demographic characteristics, section two is on pregnancy and fertility preferences, section three is on contraception services received, section four is on the perception of the quality of care received at the health facility, and the section five is on the decision-making environment. From the pilot study conducted, we anticipate initial data collection to take 20–25 min. The follow-up questionnaires are shorter with only two sections; the first section is on contraceptive history. Participants will be asked whether they are still using their baseline contraception method, any side effects and or complications experienced, and the level of satisfaction with the method. The second section will be for clients reporting discontinuation or contraceptive switching, both closed- and open-ended questions on the timing and reasons for discontinuation or switching, including fertility intention, will be asked.

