##### Data analysis

Quantitative data will be collected on RedCap [17] and cleaned before analysis to ensure completeness. Descriptive analysis of quantitative variables will be done using measures of central tendency (mean, median) and measures of dispersion (range, standard deviation), as appropriate. Descriptive statistics will be used to assess contraceptive discontinuation, including switching. Pearson’s χ2 or t test, where appropriate, will be used for univariate analyses to compare characteristics of women who continued and discontinued their initial contraceptive method. Multivariate analysis will be implemented for variables that will be significantly associated with contraceptive continuation at bivariate analysis. The time to event for this survival analysis will be calculate from method initiation to the time point when the participant reports discontinuation with her baseline method. Censoring will be done for clients lost to follow-up and those reporting discontinuation of their baseline method. Contraceptive discontinuation rates will be calculated using the Kaplan Meier survival function. Cox proportional hazard regression model will be used to estimate hazard ratio for risk of contraceptive discontinuation for independent predictors of discontinuation. The level of significance will be set at a *p*-value < 0.05. For qualitative data, the approach for data analysis will be similar to what has been presented above under the formative assessment.

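### Discontinuation is read from method status on the day of the call, so a stop and restart of the baseline method that falls wholly between two calls is not counted, and the 12- and 24-month rates may not be comparable with the calendar-based DHS reference.

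*Protocol article*

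**What the plan says.** All references are to the protocol article, Phase 2 unless noted.

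- **Outcomes** gives the event rule: "Participants will be considered to have discontinued if they report not using their baseline method during the follow-up interviews". A woman who takes up a different method within one month is classed as having switched. No rule covers a return to the same method.
- **Questionnaire** describes the follow-up instrument: "The follow-up questionnaires are shorter with only two sections; the first section is on contraceptive history". On method use it says "Participants will be asked whether they are still using their baseline contraception method"; the other items it lists for that section are side effects or complications, and satisfaction. On timing and reasons it says "The second section will be for clients reporting discontinuation or contraceptive switching".
- **Participant follow-up** sets data collection "at baseline and at 3, 6, 12, and 24 months", so the intervals between contacts are 3, 3, 6 and 12 months. It says that the 12- and 24-month period "allows comparisons with other surveys, including the DHS, that have used the same time reference to report discontinuation".
- **Data analysis** measures survival time "from method initiation to the time point when the participant reports discontinuation with her baseline method".
- **Sample size** takes 31% from the Kenya DHS as the current 12-month discontinuation rate and sizes the phase for a 10-point difference.
- **Background** says that tracking of discontinuation in Kenya is "limited to use of survey data such as a DHS that collects calendar data", that is, a history of use.

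**The concern.** Take a woman who misses resupply in month 7, goes two months without the method, restarts it in month 9 and is called at month 12. She can truthfully say that she is using her baseline method. Under the Outcomes rule she has had no event and contributes 12 months of uninterrupted use. Had her gap spanned month 6 or month 12, she would have been an event.

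The rule also treats similar women differently. One who changes to another method within a month has left her baseline method and is classed as a switcher. One who is without a method for several months and then returns to the same one is a continuous user. The plan sets a one-month limit for switching and none for resumption.

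Three features make this matter:

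- The study has a single group, and its reference is an external 31% from a survey described as collecting calendar history. No concurrent group is measured under the same rule, so a difference in event definition passes straight into the comparison.
- Within the study the error runs one way. Missed episodes can only lower the recorded rate, which is the direction the project hopes to show.
- The lapses at issue are those that the community tracking component is built to prevent. Background says that short-term users tend simply not to return for resupply, whereas implants and IUDs need a facility visit for removal. Lapses that are later resumed would drop out of the rates and out of the analysis of predictors.

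**Working it through.** **Plan's own figure.** The sample size reproduces with a pooled two-proportion formula for 31% against 21%, 80% power and a one-sided 5% test: 237 per group; 237 × 1.5 / (1 − 0.30) = 507.9, so 508; × 2 = 1016. It does not depend on the point made here. It fixes the scale: 31% reference, 10-point effect.

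**Inputs from the document.** First-stop rate 31% at 12 months (Sample size); calls at 3, 6, 12 and 24 months (Participant follow-up); the event rule (Outcomes).

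**Assumptions, not in the document.** Constant hazard; a share *r* of women who stop restart the same method; the gap is exponential with mean *m* months; no second stops (relaxed below).

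**Step 1, hazard.** λ = −ln(0.69)/12 = 0.0309 per month. First stops by 24 months: 1 − 0.69² = 52.4%.

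**Step 2, missed first stops.** A first stop in the interval (a, b] is missed if the restart comes before b. With *r* = 1, the proportion missed is

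(e^(−λa) − e^(−λb)) − [λ / (1/m − λ)] × [e^(−λb) − e^(−λa) × e^(−(b−a)/m)]

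Summed over the intervals, in percentage points:

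| Mean gap *m* | 0–3 | 3–6 | 6–12 | 12–24 | Total to 12 | Total to 24 |
|---|---|---|---|---|---|---|
| 1 month | 6.1 | 5.6 | 11.9 | 19.9 | 23.6 | 43.4 |
| 2 months | 4.3 | 3.9 | 9.8 | 18.3 | 18.1 | 36.3 |
| 3 months | 3.3 | 3.0 | 8.2 | 16.7 | 14.5 | 31.1 |
| 6 months | 1.9 | 1.7 | 5.3 | 12.7 | 9.0 | 21.6 |

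**Step 3, scale by *r*.** Shortfall = *r* × total; recorded rate = true rate − shortfall. Ranges run from *m* = 6 to *m* = 1.

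| *r* | Shortfall at 12 months | Recorded (true 31.0%) | Shortfall at 24 months | Recorded (true 52.4%) |
|---|---|---|---|---|
| 5% | 0.4–1.2 | 29.8–30.6% | 1.1–2.2 | 50.2–51.3% |
| 10% | 0.9–2.4 | 28.6–30.1% | 2.2–4.3 | 48.0–50.2% |
| 20% | 1.8–4.7 | 26.3–29.2% | 4.3–8.7 | 43.7–48.1% |
| 30% | 2.7–7.1 | 23.9–28.3% | 6.5–13.0 | 39.4–45.9% |
| 50% | 4.5–11.8 | 19.2–26.5% | 10.8–21.7 | 30.7–41.6% |

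A simulation of 400,000 women gives the same 12-month values to within 0.1 point. The shortfall grows by 24 months because the last interval is 12 months long.

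**Step 4, second stops.** If women who restart can stop again at the same hazard, some are caught at a later call. By simulation, 20% restarting with a two-month mean gap then gives 27.8% at 12 months, a shortfall of 3.2 points, against 0.20 × 18.1 = 3.6 without second stops. The figures in Step 3 are therefore on the high side.

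**Step 5, minimum gap.** Step 3 compares with counting every stop, however short. With a one-month mean gap, 1 − e^(−1) = 63% of gaps last less than a month and would not count under a one-month minimum. Against such a rule the upper ends shrink further.

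**The case against.** **The questionnaire itself is not shown.** The article summarises it in a paragraph, and its first follow-up section, asked of everyone, concerns the history of contraceptive use. A reader might infer that no item asks about gaps. That cannot be known from a summary, and a woman who volunteers a lapse might be taken through the second section. This stands. It does not cure the problem, because the stated event rule uses status at the interview and not interval history.

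**The comparator's direction is not established.** A reader might infer that the rates are shown to be too low against the DHS. The document does not support that. It does not say how the calendar codes short gaps or resumptions, and its Discussion calls calendar information prone to recall bias, so the calendar may miss brief lapses too.

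**The large magnitudes need extreme inputs.** A reader might infer that the definition alone could produce nearly the whole 10-point effect. The simple formula 0.31 × (1 − s) gives 21.7% at s = 30%, but s there is the share of all women who stop and also restart before the next call. Allowing second stops, that result needs about 45% of stoppers to resume the same method with a one-month mean gap, and nearly 60% with a two-month mean gap. Long-acting methods, 72% of Migori's method mix, are unlikely to lapse and restart unnoticed.

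**The definition may be intended.** Background describes discontinuation as abandoning a method while at risk, and a short pause may not be abandonment. That is a legitimate choice, but it then needs a stated maximum pause, and the Outcomes section has none.

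**Conclusion.** The point holds in a limited form. As written, an interruption of the baseline method lying wholly between two calls is not an event; an interruption in progress at any call is. Relative to counting every first stop, the recorded rates can only be lower, most at 24 months and mainly for resupply methods. Assuming a constant hazard and 10 to 20% of stoppers restarting after mean gaps of 1 to 6 months, the shortfall is about 1 to 5 points at 12 months (the primary outcome) and 2 to 9 points at 24 months. The restart share and gap length are assumptions, and the ranges move directly with them.

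Against the DHS, the supported conclusion is that the two rates may not measure the same event. Neither the size nor the net direction of that difference follows from the document. Even so, at 12 months a few points is a material part of a 10-point planned effect, in a single-group study that has no internal comparison to absorb it.

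**What to change.** - **Ask everyone.** At each call, ask all women, including those still using, whether they stopped the baseline method at any time since the last completed call, and in which months. If the full questionnaire already does this, say so and use it.
- **Redefine the event in Outcomes.** Count the first interruption of at least a stated minimum length, whether or not the woman has restarted by the call. Choose the minimum to match the comparator's rule and state that rule; one month, for example, would agree with the plan's own switching limit.
- **Record restarts** of the baseline method as a separate transition.
- **Keep call-day status** as a secondary measure.

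The cost is a minute or two more per call, some recall over the 6- and 12-month intervals, and a slightly less favourable rate. The Ethical considerations section notes a privacy risk from follow-up interviews for women whose partners do not know of their use, so the added items should be few. Study status places the start of enrolment in October 2019, after the article's account of progress. The change is easiest before then, because interval history that was not asked for is hard to recover later.

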##### Data analysis

Quantitative data will be collected on RedCap [17] and cleaned before analysis to ensure completeness. Descriptive analysis of quantitative variables will be done using measures of central tendency (mean, median) and measures of dispersion (range, standard deviation), as appropriate. Descriptive statistics will be used to assess contraceptive discontinuation, including switching. Pearson’s χ2 or t test, where appropriate, will be used for univariate analyses to compare characteristics of women who continued and discontinued their initial contraceptive method. Multivariate analysis will be implemented for variables that will be significantly associated with contraceptive continuation at bivariate analysis. The time to event for this survival analysis will be calculate from method initiation to the time point when the participant reports discontinuation with her baseline method. Censoring will be done for clients lost to follow-up and those reporting discontinuation of their baseline method. Contraceptive discontinuation rates will be calculated using the Kaplan Meier survival function. Cox proportional hazard regression model will be used to estimate hazard ratio for risk of contraceptive discontinuation for independent predictors of discontinuation. The level of significance will be set at a *p*-value < 0.05. For qualitative data, the approach for data analysis will be similar to what has been presented above under the formative assessment.

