##### Sample size

This phase is powered to detect a 10 percentage point difference in the primary outcome of interest— reductions in contraceptive discontinuation rates at 12 months, between baseline and endline levels with a 95% confidence interval and a power of 80%. For the purpose of the sample size calculation, Kenya DHS data was used for the current contraceptive discontinuation rate of 31% [9]. Further, the sample size is adjusted to account for a 30% attrition rate due to potential dropouts and loss of clients during follow-up through the four waves of data collection up to 24 months and a design of effect of 1.5 due to cluster sampling. This results in a total sample size of 508, which is doubled for the overall study (for the two counties), leading to 1016 women. Proportionate to size is used to allocate the sample size for each of the 10 facilities based on the current family planning caseload. Additionally, the current method mix for the two counties further determines the sample for each modern contraceptive method.

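### A p < 0.05 bivariate filter decides which predictors enter the multivariable model; it can drop masked confounders and overstates weak to moderate predictors that survive

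*Protocol article*

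**What the plan says.** The Phase 2 Data analysis section of the protocol article sets out these steps:

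- Group comparison: "Pearson’s χ2 or t test, where appropriate, will be used for univariate analyses to compare characteristics of women who continued and discontinued" their initial method.
- Entry rule: "Multivariate analysis will be implemented for variables that will be significantly associated with contraceptive continuation at bivariate analysis".
- Model for the reported effects: "Cox proportional hazard regression model will be used to estimate hazard ratio for risk of contraceptive discontinuation for independent predictors of discontinuation".
- Threshold: "The level of significance will be set at a *p*-value < 0.05".

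The same section censors women lost to follow-up in the survival analysis. The Sample size section expects such loss: "the sample size is adjusted to account for a 30% attrition rate due to potential dropouts and loss of clients during follow-up", over four waves of data collection up to 24 months. The article names no covariate that is kept regardless of significance, no looser entry threshold and no time-to-event screen. Predictors of discontinuation and switching are the third of four objectives in the Study aim section.

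**The concern.** The entry rule is a stated choice, so this is not a detail left to a fuller document. Three weaknesses follow from it.

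1. **Selection.** A weak predictor passes a 5% test mainly in samples where chance has made its effect look large. Estimates reported only for those that pass are too large on average.
2. **Masked confounding.** A variable whose effect opposes that of a correlated predictor can look null on its own and still be needed for adjustment. Correlated candidates are plausible here: the Study setting section reports that long-acting reversible methods account for 72% of the method mix in Migori and short-term methods for 64% in Kitui, so county and method type are linked.
3. **Time at risk.** A table of continued against discontinued women has no place for a woman lost at month 4. She is either excluded or counted as continuing, whereas a Cox model uses her four months.

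At stake is which factors are reported as independent predictors, and how strong they appear.

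**Working it through.** **Inputs from the protocol.** Sample size 1016 (508 per county, doubled); 12-month discontinuation 31%; attrition 30% up to 24 months; design effect 1.5; level 0.05.

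**The plan's own figure.** For 31% against 21%, with pooled variance, a one-sided 5% test and 80% power:
n = [1.645 × √(2 × 0.26 × 0.74) + 0.842 × √(0.31 × 0.69 + 0.21 × 0.79)]² / 0.10² = 237.
Then 237 × 1.5 / 0.70 = 507.9, which gives 508. A two-sided test gives 301 and then 645. Nothing below depends on this figure beyond taking 1016 as the cohort size.

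**Assumptions (not in the protocol).** Constant hazard; a binary predictor present in 30% of women; the effect sizes, correlations and loss patterns shown below.

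**Step 1. Inflation after the screen.** Chi-square screen at 0.05, then Cox; geometric mean hazard ratio (HR) among runs that pass. In both settings 30% are lost evenly over the follow-up period.

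| True HR | No screen, 12 months | Passes screen, 12 months | Reported if passed, 12 months | Reported if passed, 24 months |
|---|---|---|---|---|
| 1.2 | 1.20 | 28% | 1.39 | 1.31 |
| 1.3 | 1.29 | 51% | 1.42 to 1.43 | 1.36 |
| 1.5 | 1.50 | 86% | 1.54 to 1.55 | 1.51 |

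The 12-month columns place all 30% loss inside the first year, which is harsher than the protocol's statement. The 24-month column matches the stated attrition.

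**Step 2. Dropped confounders.** Predictor HR 1.5; a second variable present in 40% of women; the predictor is present in 55% of women with the second variable and 13% of those without. Follow-up is 12 months.

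| HR of second variable | Second variable dropped | Predictor passes | Predictor HR, full model | Predictor HR, after screen |
|---|---|---|---|---|
| 0.75 (opposing) | 85% | 53% | 1.51 | 1.47 |
| 0.67 (opposing) | 57% | 38% | 1.51 | 1.52 |
| 1.3 (same direction) | 6% | 98% | 1.51 | 1.52 |
| 1.5 (same direction) | 0.5% | 99% | 1.50 | 1.51 |

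With opposing effects, the main harm is that a real predictor with HR 1.5 is missed about half the time or more. The mean estimate moves little and can move toward 1, because selection and lost adjustment pull in opposite directions. With the HR 0.75 variable left out in every run, the predictor averages 1.31.

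**Step 3. Ignoring follow-up time.** A variable present in 40% of women affects loss only, not the hazard; loss falls in the first six months. The table shows the proportion of runs falsely significant at 0.05.

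| Loss without / with the variable | Chi-square, lost counted as continuing | Chi-square, lost excluded | Univariable Cox |
|---|---|---|---|
| 20% / 45% | 54% | 12% | 4% |
| 25% / 37.5% | 17% | 8% | 5% |
| 30% / 30% | 6% | 5% | 6% |

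The screen misleads when loss differs by predictor level, and not otherwise.

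**Step 4. Events available for a pre-specified model by 12 months.**
- No loss: 1016 × 0.31 = 315.
- 30% lost evenly within 12 months, with λ = −ln 0.69 = 0.3711 per year: 1016 × [0.70 × 0.31 + 0.30 × (1 − 0.31/0.3711)] = 1016 × (0.2170 + 0.0494) = 271.
- Divided by the design effect: 315/1.5 = 210 and 271/1.5 = 181.
- At 10 to 20 events per parameter (a rule of thumb): 181 supports about 9 to 18 parameters, and 210 about 10 to 21.
- If discontinuation falls to 21%, with λ = −ln 0.79 = 0.2357: 1016 × [0.70 × 0.21 + 0.30 × (1 − 0.21/0.2357)] = 183. Then 183/1.5 = 122, or about 6 to 12 parameters.

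Follow-up to 24 months would add events.

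**The case against.** **The reading of the screen is an inference.** The article calls the chi-square and t comparison univariate and the entry step bivariate, and does not say that they are the same. This stands as a limit on the time-at-risk point only. No other bivariate test is described, and selection and masking apply to any 5% screen.

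**Conditional inflation is not special to screening.** Picking out significant terms from a pre-specified model would inflate them in the same way. That is true, but such a model reports every named covariate, so the set of estimates is not truncated by its own p-values.

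**Several stronger readings are tempting and are not supported.**
- A reader might infer that the hazard ratios are generally biased away from 1. Inflation is trivial at HR 1.5, and dropping a masking confounder can pull an estimate toward 1.
- A reader might infer that intervals are shown to be too narrow. Selection is ignored in them, but no calculation here measures their coverage.
- A reader might place the 30% attrition within 12 months. The Sample size section spreads it up to 24 months, which lowers the inflation.
- A reader might expect confounders to be dropped routinely. Those acting in the same direction as the predictor were almost always kept.
- A reader might call the predictor list the study's main guidance for programmes. The Dissemination section mentions determinants, but also satisfaction and change in the discontinuation rate.

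**The objective is one of four.** The primary outcome is the 12-month discontinuation rate, estimated by Kaplan-Meier, and the filter does not touch it. This stands, and it limits the importance of the point.

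**Conclusion.** The concern holds for objective 3, with limited reach. The stated filter overstates surviving weak to moderate predictors: HR 1.2 becomes about 1.3 to 1.4 and HR 1.3 about 1.36 to 1.42, the lower figures applying to 24 months of follow-up and the higher to 12. At HR 1.5 the effect is negligible (1.51 to 1.55). The filter can also discard a confounder that opposes a correlated predictor, and with it the predictor. How often depends on an assumed correlation and effect that the protocol cannot confirm. The time-ignoring screen does harm mainly if loss differs across predictor levels. All sizes rest on a constant hazard, a binary predictor with 30% prevalence, and simulation without clustering. The 12-month primary rate and the sample size are unaffected. This is a change that should be made, not one on which the study's validity turns.

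**What to change.** Replace the significance filter with a Cox model whose covariates are named before cohort data are analysed and kept regardless of p-value.

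- Choose them from subject knowledge and the Phase 1 formative work. Examples are method type, county, age, fertility intention and the method information index.
- Add other items only once they are confirmed to be on the baseline form. The Questionnaire section describes its five sections but does not itemise the questions.
- Count parameters, not variables, and limit them to what roughly 180 to 210 effective events by 12 months can support, or about 120 if discontinuation falls to 21% and 30% are lost within the year.
- Show univariable Cox hazard ratios beside the adjusted ones for description only, in place of chi-square or t tests, and do not let them decide entry.

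The cost is a change of analysis wording and slightly wider intervals from keeping weak covariates. The proposed examples need no new data, subject to the check against the baseline form.

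### Discontinuation is dated when it is reported, not when it happened: event times run late, and the 12-month rate can be understated, by nothing to about 14 points depending on call timing

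*Protocol article*

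**What the plan says.** All the relevant text is in the Phase 2 part of the protocol article's Methods.

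- **Event time** (Data analysis): "The time to event for this survival analysis will be calculate from method initiation to the time point when the participant reports discontinuation".
- **Event** (Outcomes): "Participants will be considered to have discontinued if they report not using their baseline method during the follow-up interviews".
- **Schedule** (Participant follow-up): "Data collection will occur the following time points: at baseline and at 3, 6, 12, and 24 months". For each round, "three attempts will be made to contact participants before a determination of loss to follow-up is made". No call window is stated.
- **Primary outcome** (Outcomes): "The primary outcome of this study is the contraceptive discontinuation rate among the family planning users at 12 months". Participant follow-up ties it to a visit: "The follow-up at 12 months will be used to determine the contraceptive continuation rate, which is the primary outcome for this study".
- **Estimator** (Data analysis): "Contraceptive discontinuation rates will be calculated using the Kaplan Meier survival function". No interval-censored method is named.
- **Data on stop times** (Questionnaire): women who stopped or switched are asked "both closed- and open-ended questions on the timing and reasons for discontinuation or switching".

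**The concern.** The event-time rule and the event definition together place each stop at the interview where it comes to light. The true stop lies somewhere between that interview and the one before it, and the gap just before the primary time point is 6 months. The article collects the information needed to do better, but its analysis rule does not use it. Its own definition of switching, which turns on starting another method within one month of stopping, already needs a stop date and cannot be judged from interviews 3 to 12 months apart.

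Two things are at stake. First, the curve between visits and the Cox event times used to study predictors are late and heaped on a few dates. Second, a delay can carry a stop that occurred before month 12 past month 12, but cannot do the reverse. Any effect of the delay on the 12-month rate is therefore downward, which flatters the programme against the 31% reference taken from the national survey.

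**Working it through.** **Inputs from the article.** Interviews at 3, 6, 12 and 24 months (Participant follow-up). Reference 12-month discontinuation of 31% and a 10-point target difference, so 31% to 21% (Sample size).

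**Assumptions, because the article gives neither.** The hazard is constant, or falling as a Weibull with shape 0.7. Call-timing patterns are as listed below. Discontinuation is treated as the event.

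**1. The plan's own figure.** Comparing 31% with 21% at one-sided 5% and 80% power needs 237 women. Then 237 × 1.5 = 355.5, and 355.5 / 0.70 = 507.9, which gives the stated 508 per county. This does not depend on how events are dated. Here it only fixes 10 points as the yardstick.

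**2. Lag in the event times.** A stop is dated at the next interview, so the lag is up to 3 months for stops before month 6, up to 6 months for stops between months 6 and 12, and up to 12 months for stops between months 12 and 24. Late calls add to this.

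**3. The most that can move past month 12 if the 12-month call is completed.** This is the share of women who stop between months 6 and 12.

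- Constant hazard, true rate 31%: F(6) = 1 − 0.69^0.5 = 16.9%, so 31.0 − 16.9 = 14.1 points.
- Weibull shape 0.7, true rate 31%: F(6) = 1 − 0.69^(0.5^0.7) = 20.4%, so 10.6 points.
- True rate 21%: F(6) = 11.1% and 9.9 points (constant hazard), or 13.5% and 7.5 points (Weibull 0.7).

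**4. How much does move.** The table gives the Kaplan-Meier estimate of discontinuation at 12.0 months with events dated at the report and a true rate of 31% (40,000 simulated women per scenario, simulation error about 0.3 points).

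| Call timing | Constant hazard | Weibull 0.7 |
|---|---|---|
| Exactly on schedule, or nominal wave times | 31.0% | 31.1% |
| 0 to 1 month early | 29.9% | 30.0% |
| Within ±0.5 month | 24.2% | 25.9% |
| 0 to 1 month late | 18.5% | 21.6% |
| On schedule, but 10% miss month 12 and report at month 24 | 29.8% | 29.6% |

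Hand checks for constant hazard, using average call times:

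- Early: the 12-month call falls at 11.5 months on average, and 1 − 0.69^(11.5/12) = 29.9%.
- Scattered: half the women are called before month 12, at 11.75 months on average, and half after. 0.5 × 30.5 + 0.5 × 16.9 = 23.7%.
- Late: only stops before the 6-month call, at 6.5 months on average, are counted. 1 − 0.69^(6.5/12) = 18.2%.
- Missed calls: 0.10 × 14.1 = 1.4 points, or 0.10 × 10.6 = 1.1 points with the falling hazard.

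Adding 30% loss to follow-up changed the constant-hazard results for early, scattered and late calls by less than 1 point.

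**5. With the event at the true stop time.** The estimate is about 31% (or 21%) under every call pattern.

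**The case against.** The strongest reply is that the primary outcome belongs to the 12-month wave. Participant follow-up says that this visit determines it, and Outcomes counts a woman as discontinued if she reports non-use at a follow-up interview. The article also calls the scheduled 3, 6, 12 and 24 months its time points. If event time takes only those nominal values, a woman who stops in month 7 and says so at her 12-month interview has an event at 12, and Kaplan-Meier at 12 counts it. This argument stands: under that reading the 12-month rate is not biased, apart from women who skip the 12-month call. The rates at 3, 6 and 24 months are likewise correct at the visit times when waves are complete, so it would be wrong to infer that nominal timing still shifts them.

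A second reply is that the rule might mean the stop date the woman reports. That is possible but less natural beside the event definition, and if it is intended the wording still needs to say so.

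A third is that an article leaves call windows and date derivation to fuller documents. That is fair for the windows, but the event-time rule is stated here, and as stated it passes over the timing data. Ties in the Cox model are minor, since standard methods handle them.

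None of this removes the late event times between visits or the late dating of women who first report at month 24.

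**Conclusion.** The event-time rule should be replaced. As written it makes event times late by up to 6 months before month 12 and up to 12 months after it. That distorts the between-visit curve and the Cox event times however the calls are timed.

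For the primary rate the effect is conditional and downward:

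- about zero with nominal wave times or calls on or before month 12 (about 1 point if calls are up to a month early);
- about 1 point per 10% of women who miss the 12-month call and report at month 24;
- up to about 14 points (constant hazard) or 11 points (Weibull shape 0.7) at a true rate of 31%, if actual call dates fall after month 12 and the curve is read at 12.0 months.

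The upper end is as large as the 10-point target. A reader might infer that the 12-month rate is certain to be understated by 7 to 14 points. The article does not support that: it does not say whether nominal or actual dates are used, gives no distribution of call times, and links the primary outcome to the 12-month visit. The range starts at zero, and the figures rest on assumed hazards and call patterns.

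**What to change.** Define event time as method initiation to the stop date (month) that the woman gives in section 2 of the follow-up questionnaire. Constrain it to lie between the last interview at which she was still using the baseline method and the interview at which she reported stopping. Where the date is missing, treat the event as interval-censored between those two interviews. Run an interval-censored analysis (Turnbull) or a discrete-time one (complementary log-log) as a sensitivity check on the 12-month rate and the predictor model. State the call window for each round.

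The cost is a change of wording and slightly more analysis, with no new data collection. The downside is some recall error in the reported month, which the bounding interviews limit.
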